
### Primary outcome

The time between starting medication and body temperature returning to normal (oral temperature 37.2°C and maintain 24 hours).

### Secondary outcomes

1. The recurrence rate of fever after momentary recovery: the incidence of fever recurrence (oral temperature > 37.2°C) within 24 hours after the patient’s temperature has normalized after treatment;2. The negative rate of RATs at day 14 and the negative conversion time (two successive negative RATs result with at least 24 hours interval);3. The remission rate of major symptoms at day 14 (oral temperature ≤ 37.2°C, score of cough and fatigue ≤ 1 (“None”, “Mild”, “Moderate”, “Severe” and “Very severe” were marked as 0 to 4 450 respectively), and continues 24 hours);4. Time of major symptoms remission: time from the start of treatment to symptoms remission (definition of symptoms remission: oral temperature ≤ 37.2°C, cough and fatigue score ≤ 1 and lasting at least 24 hours);5. The disappearance rates at day 14 and disappearance time of symptoms: the disappearance rates and time of individual symptoms of mild and moderate COVID-19 within 14 days (time defined as the period between starting medication and symptom disappearance); 6. The rate of patients whose oxygen saturation had gone below< 94% after intake of drugIMP, measured at day 14;7. Incidence of the progression to severe or critical illness during the trial;8. All-cause mortality at the 21st day after stopping the medication;9. Utilization rates of antipyretic, Paxlovid and molnupiravir within 14 days and the total dosage(s) of the drug(s) used.

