### Study outcomes

#### Assessment

1. The time between starting medication and body temperature returning to normal and the recurrence rate of fever after momentary recovery. Each subject will be issued with the same type of oral thermometer for measurement at 9 a.m. (±2 h) and 9 p.m. (±2 h) daily, with at least 12 h between each measurement. Normal oral temperature is defined as equal to or below 37.2°C. Temperature recovery time is defined as the total number of days between medication starting date and the date of “normal oral temperature for 24 h without antipyretic” (both days inclusive). Subjects are required to measure the temperature until day 14 or on the day when the temperature has remained normal for 24 h, whichever is later.2. The negative rate of RATs at day 14 and negative conversion time. Each subject will be issued with the same type of RAT kits which can be used for at least 14 days for testing at 9 a.m. (±2 h) each day, with at least 24 h between each test. Negative conversion time is defined as the total number of days between the medication starting date and the date of securing two successive negative RAT results (both days inclusive). Subjects were required to undergo testing until day 14 or the day when two successive negative RAT results at least 24 h apart are obtained, whichever is later.3. The remission rate at day 14 and remission time of major symptoms.4. The disappearance rates at day 14 and disappearance time of symptoms. Subjects are required to record the status of their symptoms including major clinical symptoms daily at 9 p.m. (±2 h). Except for fever which is marked as ‘No’ or ‘Yes’ according to whether the oral temperature exceeds 37.2°C, other symptoms will be graded on a scale of 0–4 from “None”, “Mild”, “Moderate”, “Severe” and “Very Severe” depending on the actual feelings of the subject (“None” means the symptom is not present, “Mild” means the symptom is present but does not interfere with daily activities; “Moderate” means the symptom is present and slightly interferes with daily activities; “Severe” means the symptom is present and most daily activities cannot be done; “Very Severe” means the symptom is present and interferes with all daily activities). Major clinical symptoms include fever, cough and fatigue. Remission is defined as oral temperature ≤37.2°C, cough and fatigue score ≤1; disappearance is defined as the symptom being present at day 0 (score >0) but the symptom score is 0 at the date of recording.5. All-cause mortality at the 21st day after stopping the medication.6. Incidence of the progression to severe or critical illness during the trial. The all-cause mortality at the 21st day after stopping the medication and the incidence of the progression to severe or critical illness during the trial will be confirmed by communication with the subjects and/or other related person(s) or checking their medical record in the Hospital Authority. The definitions of severe and critical illness are based on the related definitions of “Coronavirus disease 2019 (COVID-19) Treatment Guidelines” published by National Institutes of Health (severe illness: oxygen saturation in the indoor environment of sea level <94%, oxygenation index [PaO2/FiO2] < 300 mmHg, respiratory frequency >30 breaths/min, lung infiltrates >50%; critical illness: respiratory failure, septic shock, and/or multiorgan dysfunction or failure).7. Utilization rates of antipyretic, Paxlovid and molnupiravir within 14 days and the total dosage(s) of the drug(s) used. In this study, subjects are allowed to take western medicines prescribed for the treatment of COVID-19 under the current guidelines of the Hong Kong Hospital Authority with at least 2 h’ gap between Chinese and western medicines. If oral temperature >39.0°C and continues over 4 h; or the oral temperature >39.5°C, the patient is advised to take antipyretic (paracetamol is recommended as a priority) for acute treatment. Patients need to record the amount and time of the drug(s) used.8. Oxygen saturation. For safety reasons, each subject will be issued with the same type of pulse oximeter for measurement at 9 a.m. (±2 h) and 9 p.m. (±2 h) daily, or whenever the subject decides it is necessary. If the reading is less than 94%, the patient is considered to have severe illness and has reached the end point of the study and is recommended to seek medical attention immediately. Subjects are required to measure their oxygen saturation at rest until day 14 or the time of body temperature returning to normal (continuing for 24 h) or the negative conversion time (2 successive negative RAT results), whichever is later.

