### Sample size and statistical methods

#### Sample size estimation

The primary outcome of the study is the time between starting medication and body temperature returning to normal, i.e., the time to fever resolution after the first treatment. Based on previous studies, we assumed the standard deviation (SD) is 0.7, and the time to fever resolution of half a day (0.5 days) would have clinical significance (Qiu et al., 2020; Chen et al., 2021). Therefore, to detect such a difference between groups, 38 in each group will be needed with a power of 80% and a 5% 2-tail significance level. To allow for possible dropouts during the study period, we inflate this value by 20%, hence a total of 96 patients will be needed for the proposed study and 48 in each group (12 in each sub-group).

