#### Statistical analysis

Basic demographic data (gender, age, *etc.*) will be descriptively summarized. Continuous variables are presented as mean ± standard deviation (SD) and categorical variables are presented as ratios. Intra group comparisons between baseline and each visit will be conducted by using paired *t*-test (or Wilcoxon signed rank test). Linear mixed model will be used to compare the outcomes between groups. All statistical tests will be two-sided, and *p* < 0.05 is considered significant difference. The statistical analysis will be done by an independent statistician and all analysis will be conducted by SPSS. If there is a significant difference in the use of western medicines between the treatment and control groups, it will be considered and processed as a covariance in the statistical analysis.

In this study, the subject will be deemed as “per protocol” if they have taken the maximum dose or if they stop until getting negative RAT results on two successive days and the major symptoms subside (defined as oral temperature ≤37.2°C, the score of cough and fatigue ≤1) with ≥85% intake compliance. The intake compliance is calculated by dividing the no. of packs of drugs ingested by either:a) the number of packs of core formula the subject should take daily (daily dose) x the number of days from the day of starting drug intake to the day the drug is stopped according to the criteria (e.g., if the subject should take 4 packs of core formula a day, starts taking drug on 1 January, stops at 8 January according to criteria, and has taken 30 packs, the compliance will be (30/(4 × 8)) x 100%) = 93.75%, with the subject deemed as “per protocol”; orb) daily dose x 14 for all other cases (e.g., if the subject should take 4 packs of core formula a day, starts taking drug in 1 January and stops at 3 January because of adverse events, and has taken 12 packs, the compliance will be (12/(4 × 14)) x 100%) = 21.43%, with subject deemed as not “per protocol”.

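### Cough and fatigue are graded 0–4 every day, but every listed between-arm symptom outcome uses only a cut at ≤1 or 0; adding the graded score would gain roughly 10 to 20 points of power over the listed time outcomes, and more over the day-14 rates

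*Protocol article*

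**What the plan says.** Under Assessment, fever is recorded as yes or no, and "other symptoms will be graded on a scale of 0–4 from" none to very severe. The levels are defined by interference with daily activities, and scores are entered once a day at about 9 p.m. Fever, cough and fatigue are the major symptoms, and the Hypothesis is superiority over placebo on the major symptoms.

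Under Secondary outcomes, the symptom items are:
- Item 3: "The remission rate of major symptoms at day 14 (oral temperature ≤ 37.2°C, score of cough and fatigue ≤ 1", sustained for 24 hours.
- Item 4: time to that same remission state.
- Item 5: "The disappearance rates at day 14 and disappearance time of symptoms", where the Assessment section defines disappearance as a score of 0 in a subject who scored above 0 on day 0.

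No mean score, change in score or area under the curve is listed. For between-group comparisons, Statistical analysis says only: "Linear mixed model will be used to compare the outcomes between groups".

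**The concern.** Two of the three major symptoms reach the between-arm comparison only as threshold crossings. A fall from 4 to 2 counts for nothing in any listed item, and a fall from 1 to 0 counts only in item 5.

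The entry criteria weaken the remission items further. Cough ≥2 and fatigue ≥2 are alternatives to fever for dating symptom onset, while a raised temperature is required at screening. A subject may therefore enter with both scores already at ≤1. For that subject, remission of major symptoms is simply fever resolution, which is the primary outcome again.

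A rate read at day 14 is also late for mild to moderate illness with at most 72 hours of symptoms at entry. If most placebo subjects have recovered by then, the rate cannot separate the arms however much sooner treated subjects improved. A null result could then be taken as no effect on cough or fatigue. The named model and the listed symptom outcomes also fit poorly: the model suits repeated scores, and the listed outcomes are rates and times.

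**Working it through.** **1. Group size.** The plan assumes a difference of 0.5 day ("the time to fever resolution of half a day (0.5 days) would have clinical significance"), "we assumed the standard deviation (SD) is 0.7", and sizes the trial "with a power of 80% and a 5% 2-tail significance level". The normal formula gives 2 × (1.96 + 0.842)² × 0.7² / 0.5² = 30.8, so 31 per arm (32 with the t distribution). The plan states "38 in each group will be needed", which these inputs do not reproduce. That is a separate point; 38 is used below only as the evaluable number per arm. No power is stated for any symptom outcome.

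**2. The fever part of the day-14 rate.** With the plan's SD of 0.7 day, three SDs below day 14 is 14 − 3 × 0.7 = 11.9 days. Unless mean fever time approaches 12 days, nearly everyone is afebrile by day 14 in both arms, so this component adds almost no information.

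**3. How a rate behaves near its ceiling.** Two-proportion test, 38 per arm, two-sided 5%, with assumed rates:
- 80% v 90%: 23% power
- 90% v 95%: 13% power
- 95% v 97.5%: 8% power

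**4. Simulation of the daily scores.** The documents give no cough or fatigue distribution, so every input here is assumed.
- Latent score = b × exp(−t/τ), with b of mean 2.2 and SD 0.8.
- Placebo τ is 4, 6 or 9 days, with a log-SD of 0.5 between subjects, shared by both symptoms.
- Daily error has SD 0.5; the result is rounded and limited to 0–4.
- Treatment multiplies τ by 0.65 (35% shorter) or 0.75 (25% shorter).
- Scores are complete to day 14, and temperature is taken as normal.
- Remission means both scores ≤1 on two successive days. Cough disappearance means two successive zeros.
- Placebo day-14 remission comes out at about 97%, 92% and 80% for the three values of τ.
- The score analysis is an ANCOVA of the mean score over days 1–14 on the day-0 score, a simple stand-in for the mixed model. Under no effect it rejected in 4–6% of runs.

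Power at 38 per arm, as the range over the three values of τ:

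| Analysis | 35% shorter | 25% shorter |
|---|---|---|
| Day-14 remission rate (chi-square) | 1–38% | 1–20% |
| Time to remission, or to cough disappearance (log-rank) | 63–66% | 33–35% |
| Mean daily score, one symptom | 76–79% | 42–43% |
| Mean daily score, cough plus fatigue | 87–89% | 50–54% |

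The lowest day-14 figures occur where placebo remission is nearest 100%.

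**5. Gain over the listed time outcomes**, lower ends and upper ends compared in turn:
- One symptom: 76 − 63 = 13 and 79 − 66 = 13 points at the larger effect; 42 − 33 = 9 and 43 − 35 = 8 at the smaller.
- Combined score: 87 − 63 = 24 and 89 − 66 = 23 points; 50 − 33 = 17 and 54 − 35 = 19.

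**6. Sensitivity to the assumptions.** A second model used placebo median half-lives of 2 to 6 days, symptoms only partly correlated, and recovery 1.6 times or 1.35 times as fast. The results, in that order, were:
- Day-14 remission rate: 0–35% and 0–21%
- Day-14 cough disappearance rate: 7–42% and 6–23%
- Time to remission: 76–78% and 40–43%
- Time to cough disappearance: 71–73% and 35–39%
- Combined mean score: 96–98% and 67–70%

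The ranking is the same. The gap between combined score and time to remission is 96 − 76 = 20 points at the larger effect and 67 − 40 = 27 at the smaller.

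**The case against.** A reader might infer that most of the power on cough and fatigue is lost. The documents do not support that. Items 4 and 5 also list time to remission and time to disappearance of individual symptoms. Both draw on the daily record, and in the main simulation they keep most of the power of the graded score (for example 63/87 = 72% of the combined score's power at the larger effect, and 33/50 = 66% at the smaller).

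A reader might also infer that the day-14 rates are known to sit near their ceiling. The article gives no symptom rates. The ceiling is plausible for remission but less so for the score-0 cut, where the assumed placebo rate for cough in the second model was 0.53–0.86.

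Other points on the plan's side:
- The cuts have clinical meaning. A score of 1 is a symptom that does not interfere with daily activities, 0 is absence, and ≤1 matches the definition of subsided symptoms under Study medications. This stands, and is a reason to keep the recovery outcomes.
- Statistical analysis plans paired tests from baseline to each visit, which could use the scores. Those are within-group tests and do not compare the arms.
- The choice of score for the mixed model could be left to an analysis plan. That is fair for model details, but the list of secondary outcomes is fixed here and contains no graded score.
- These are secondary outcomes for which no power is claimed. This stands, and limits the weight of the point.
- Follow-up assessment can be read as letting daily scoring end at temperature or antigen-test recovery. Scores would then be missing according to recovery, which the simulations do not model. This stands, and the fix has to deal with it.

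**Conclusion.** The point holds in limited form. The plan collects a five-level daily score and compares it between arms only through cuts at ≤1 or 0, while naming a model that suits the score itself. Severe loss of power is confined to the day-14 rates, and its size depends on how high placebo recovery is by day 14. Against the listed time outcomes the graded score gains about 10 to 20 points in the main simulation: toward the lower end for a single symptom, and around or slightly above the upper end for the combined score.

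The direction was the same in every scenario run. The sizes rest on assumed symptom courses, complete scores to day 14 and 38 evaluable subjects per arm. The primary outcome and the sample size are not affected. The improvement is worthwhile and cheap, and its absence does not invalidate the trial.

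**What to change.** 1. Under Secondary outcomes, add a between-arm comparison of the baseline-adjusted daily 0–4 cough and fatigue score over days 1–14. The combined score is preferable, with each symptom also shown.
2. Analyse it with the linear mixed model already named, as repeated measures with treatment, day, treatment-by-day and baseline score, and report the average difference over days 1–14.
3. Keep time to remission and time to disappearance. The new outcome adds to them and does not displace them.
4. Report the day-14 rates with confidence intervals, and state that a null rate will not be read as no effect on cough or fatigue.
5. Under Follow-up assessment, state that symptom scoring runs to day 14 for every subject and that the day-0 baseline score is taken before the first dose. At present scores are entered at about 9 p.m., and both medication and the daily record start on day 0, so the day-0 score may follow dosing.

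The cost is a few more diary entries from subjects who recover early and one more model. A mean score is also less direct clinically than recovery, which is why the recovery outcomes stay. No extra subjects or visits are needed.

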### Safety index:

1. Oxygen saturation;

2. Rate of adverse events

### Sample size and statistical methods

#### Sample size estimation

The primary outcome of the study is the time between starting medication and body temperature returning to normal, i.e., the time to fever resolution after the first treatment. Based on previous studies, we assumed the standard deviation (SD) is 0.7, and the time to fever resolution of half a day (0.5 days) would have clinical significance (Qiu et al., 2020; Chen et al., 2021). Therefore, to detect such a difference between groups, 38 in each group will be needed with a power of 80% and a 5% 2-tail significance level. To allow for possible dropouts during the study period, we inflate this value by 20%, hence a total of 96 patients will be needed for the proposed study and 48 in each group (12 in each sub-group).

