#### Baseline randomization (day −1 or 0)

Eligible subjects will be assessed by our registered CMPs via telemedicine in this trial, during which medical history and concomitant medication will be recorded. After stratification, subjects will be randomly assigned in a 1:1 ratio to receive up to 14 days of either modified Yinqiao Powder-Maxing Ganshi Decoction (about 33.4–59.7 g each day) or placebo granules (about 33.4–59.7 g each day). Specifically, the stratified randomisation is based on age (A: “18–49 years old” and B: “50–65 years old”) and the number of vaccination (a: “received 3 or more doses - fulfilling government vaccination requirement” and b: “received 2 doses or less of vaccine - yet to be fully vaccinated”). Subjects will be divided into two groups by age: one group is “18–49 years old” and the other one is “50–65 years old”; then they will be further divided into two groups within the different age group by the numbers of vaccination: one group is “received 3 or more doses of vaccine, and the another is “received 2 doses or less of vaccine”. Four subgroups will be created after stratification and subjects in each subgroup will be randomly assigned to either the treatment or placebo group. The distribution of age and number of vaccinations between the two groups will be roughly comparable after stratified randomisation. The IMP will be prescribed by Registered CMPs and will be sent to patients by delivery service. The current Western medicine treatment can continue during the study period.

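### The printed inputs give 31 or 32 evaluable patients per group, not 38; at 38 the power is about 87%, so the stated power, size or an input is wrong

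*Protocol article*

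**What the plan says.** The calculation stands in the protocol article under Sample size estimation. The outcome is the time from starting medication to normal body temperature. The inputs, attributed to earlier studies, are these:

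- Variability: "we assumed the standard deviation (SD) is 0.7". No unit is given; days is implied by the difference.
- Difference to detect: "the time to fever resolution of half a day (0.5 days) would have clinical significance".
- Result: "38 in each group will be needed with a power of 80% and a 5% 2-tail significance level".
- Dropout: "we inflate this value by 20%, hence a total of 96 patients will be needed for the proposed study and 48 in each group".

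Under Baseline randomization, "subjects will be randomly assigned in a 1:1 ratio". The sample size section names no test, formula or software, and no adjustment other than dropout. Under Statistical analysis, groups are to be compared with a linear mixed model. A Wilcoxon test appears there only as an alternative for within-group comparisons with baseline. There is one primary outcome.

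**The concern.** The article gives every input that a comparison of two means needs and presents 38 as their consequence. A reader can therefore redo the sum, and it does not come out: 38 is 6 or 7 patients per group above the answer, roughly a fifth, which is more than rounding of the result can explain.

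This figure is the trial's only stated justification for its size. If the inputs are right, the power is misstated. If the power is right, some input is not the one used, and the reader is misled about the SD or the effect for which the trial was planned. The two cases differ in practice: an SD of about 0.77 instead of 0.7 uses up the whole apparent margin above 80%.

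**Working it through.** **Inputs.** SD 0.7, difference 0.5, power 80% and two-sided alpha 5% (Sample size estimation); 1:1 allocation (Baseline randomization). Standardised difference: 0.5/0.7 = 0.714.

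**Attempt to reproduce 38, normal approximation.**

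n per group = 2 × (z₀.₉₇₅ + z₀.₈₀)² × (SD/difference)² = 2 × (1.960 + 0.842)² × (0.7/0.5)² = 30.8, rounded up to **31**.

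**Two-sample t-test (noncentral t).** The solution is 31.76, rounded up to **32**. Neither method gives 38.

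**Power at the printed SD and difference, two-sided 5%.**

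| Evaluable per group | t-test | Normal approximation |
|---|---|---|
| 31 | 79.0% | 80.3% |
| 32 | 80.3% | 81.5% |
| 38 | **86.7%** | 87.6% |

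**What would make 38 right at 80% power?** By the t-test, an SD of 0.768 with the difference at 0.5, or a difference of 0.456 days with the SD at 0.7. The normal approximation gives 0.778 and 0.450. In round terms: SD about 0.77, or difference about 0.46 days.

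**Does a common variant give 38 with the printed SD and difference?**

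| Variant | Per group | Stated in the article? |
|---|---|---|
| One-sided 5%, 80% power | 25 (normal) | No; two-sided is stated |
| 85% power | 36 (normal), 37 (t) | No |
| 90% power | 42 (normal), 43 (t) | No |
| Rank test, efficiency 0.955 | 32/0.955 = 33.5, so 34 | No between-group rank test |
| Rank test, worst-case efficiency 0.864 | 32/0.864 = 37.04, so 38; from the unrounded 31.76, 36.8, so 37 | No between-group rank test |
| Two-sided alpha 2.5% | 38 (normal), 39 (t) | No; 5% is stated |

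The variants that reach 38 each add something that the article does not say or that it contradicts.

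**Dropout step.** To keep 38 evaluable after 20% loss: 38/(1 − 0.20) = 47.5, rounded up to 48 per group and 96 in total. This agrees with the article.

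**The case against.** The strongest reply is that only non-reproducibility has been shown. The section names no test or software, and ordinary choices come close to 38: a rank test at worst-case efficiency, or an SD rounded to one decimal. An SD of 0.749 would print as 0.7, needs 36.2 (so 37) per group by the t-test, and gives 81.9% power at 38. A condensed article may leave such detail to the full protocol. The discrepancy is also in the safe direction and touches neither type I error nor any estimate.

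Much of this stands. It means that an input, rather than the power or the size, may be what is wrong, and that the trial cannot be called underpowered on this ground. It does not rescue the sentence. The article does not merely omit a detail; it prints inputs and draws from them a result that they do not give. None of the explanations is in the text, and the rank-test one sits poorly with the linear mixed model planned between groups.

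A reader might infer three further things that the article does not support:

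- **That dropout was counted twice**, because 32 × 1.2 = 38.4. Nothing in the section suggests two inflations. The idea needs multiplication in one step and division in the next, and 38.4 rounds up to 39.
- **That 48 is wrong**, because 38 × 1.2 = 45.6. Dividing by 0.8 is the standard way to retain 38 after 20% loss, and it gives 48.
- **That the trial enrols 16 patients too many**, because 32/0.8 = 40 per group, or 80 in total. This holds only if the printed SD is exact, and the article does not let one check that.

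**Conclusion.** The sentence is wrong as written. The printed SD, difference, power and alpha give 31 (normal approximation) or 32 (t-test) per group with 1:1 allocation, not 38. At 38 evaluable per group the power is about 87%. The stated power, the stated size or a stated input is therefore wrong, and the document does not show which.

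At the printed inputs the error is conservative, by about 7 percentage points of power. If the true planning SD was about 0.77, there is no surplus at all. This is a fault of reporting and reproducibility in the figure that justifies the trial's size, and it gives no ground for changing enrolment.

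The conclusion assumes a comparison of two means with a common SD, with the 0.7 in days. That is the calculation which the printed inputs describe.

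**What to change.** Keep 96 patients and restate the sentence under Sample size estimation, for example:

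> 38 evaluable patients per group (48 randomised per group, 38/0.8, allowing for 20% dropout) give about 87% power to detect a difference of 0.5 days at an SD of 0.7, with a two-sided 5% significance level, and 80% power if the SD is about 0.77.

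If a different SD, difference, alpha or test was in fact used to obtain 38, print that in place of the present input and name the method.

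The cost is one sentence. Enrolment, allocation and conduct do not change.
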